## 10. Statistical plan and data analysis

### 10.1 Sample size estimation

An unpublished dataset of cerebral NIRS oximetry in 23 extremely preterm infants monitored from the first hours after birth until 72 hours after birth by the INVOS 4100 NIRS device in Utrecht during the period January 2004 until January 2008 was used to estimate the sample size (unpublished data). The cerebral saturation was recorded in 5 second-values. The data were censored by the proprietary Signal Base software. The recording was reliable 79% of the time, ranging from 48% to 97%. The time spent with a cerebral saturation below 55% and above 85% was calculated and the burden of hypo- and hyperoxia was calculated by summing the percentage deviation over time area under the curve – AUC). The burden of hypo- and hyperoxia was corrected for the loss of recording time and expressed as %hours per 72 hours.

There was a relatively high correlation between time spent in hypoxia and the burden of hypoxia. Overall, hyperoxia was only about 10% of hypoxia. There was a trend towards inverse correlation between hypoxia and hyperoxia. The distribution of AUC outside the range was skewed towards the right (higher values). The mean was 76.0%hours  $\pm$  SD of 83.2. After a log-transformation, the distribution was not significantly different from normal. The mean was 1.64  $\pm$  SD of 0.50 (Figure 4).

[figure not shown]

Figure 4: The distribution of the primary outcome burden of hypo-and hyperoxia expressed as %hours and transformed logarithmically

As a result, the statistical distribution has to be normalised by logarithmic transformation. Reducing the duration of time with hypoxia or hyperoxia by 0.30 (corresponding to a 50% reduction of the time with hypoxia or hyperoxia) with a type I error (alpha) of 5% and a type II error of 0.05 (power of 95%) requires randomisation of a total of 150 preterm infants (or 'pair' or 'groups of infants' in case of multiple births): 75 preterm infants in the experimental group and 75 preterm infants in the control group.

However the prevalence of twins among extremely preterm infants is about 30%. The within cluster correlation diminishes the statistical power. To account for this the sample size needs to be multiplied by the 'design effect' (50):

$$\text{Design effect} = 1 + (n' - 1) \times \text{ICC}$$

ICC = intraclass correlation coefficient

$n'$  = average cluster size

The twin ICC is unknown for cerebral oximetry. A pragmatic solution is to increase the sample size to 166 in present study with a continuous outcome and only about 30% of infants in clusters of two. This corresponds to a ICC of 0.33.

## 10.2 Data analysis and statistical methods

All analyses will be intention to treat analyses conducted blinded with two sided tests at the 0.05 level of significance.

The statistical analysis is complicated by the fact that up to 30% of the births may be twin or triplet births where participating siblings will be randomized to the same arm creating multiple clusters of two observations that may be correlated. Shaffer et al (51) found that for this type of data without covariates added a mixed effects model with random intercept is the preferred model for continuous outcome data while ordinary logistic regression is preferred for binary data. Sauzet et al (52) studied the effect of including adjusting covariates in the model for a continuous outcome variable. They found not negligible and similar bias for estimated coefficients whether a mixed model or a linear regression model was used. Standard errors were underestimated using linear models thus inflating the type I error.

A mixed model with random intercept for continuous outcome variables and ordinary logistic regression for binary (and ordinal) outcome variables will be used. The analyses will be adjusted for the protocol specified variables (gestational age category and trial site indicator) and (following multiple imputations if necessary) will be the primary results. Since the intra cluster correlation may cause parameter estimate bias in the presence of covariates

(other than the intervention indicator) for continuous outcome variables an unadjusted analysis will also be done. If the results of the adjusted and unadjusted analysis differ markedly the results will be discussed. The effect of covariates is unknown for binary outcome variables.

If for a specified statistical model to be used in one of the above analyses of primary and secondary outcome measures Little's test is significant ( $p < 0.05$ ) and the percent missing cases  $> 5\%$  multiple imputations will be applied to adjust for values missing at random (SPSS version 17 or later).

To assess the spectrum of potential bias resulting from data missing not at random the following sensitivity analysis will be done for the primary outcome measure: let A be the group with a beneficial effect (low outcome value) as compared to the other group (group B), min be the minimum value, and max the maximum value in the material. Two estimates of the coefficient (c) of the intervention indicator will then be calculated where missing values in A are replaced by the maximum value found in the material and missing values in B are replaced by minimum value found in the material and vice versa. Since the imputation may impact the standard error of the parameter estimate in an unpredictable way the standard error of the primary analysis will be used in each case to test if the estimate deviates significantly from 0.

The null hypothesis corresponding to the primary outcome measure is tested at the 0.05 level of significance. If the test is significant the three secondary outcomes (IBI at 64 hours, cUS, all cause mortality at term) will be tested using  $\alpha = 0.05$  and Hommel's procedure as adjustment for multiplicity (53).

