### 1.5.1 NIRS devices

Different NIRS devices differ in absolute values and in dynamic ranges (32). There is no 'reference standard' for tissue oximetry. Therefore, comparison of devices can be done in a standardised setup in the forearm of healthy adults. Reproducibility is assessed by re-siting of the sensors during steady state and a test of dynamic range is done by arm exercise and subsequent arterial occlusion by a cuff. Four devices have been compared in a preliminary study:

- NIRO 200 NX;
- NIRO 300;
- INVOS 5100c; and
- OxyPrem (a prototype).

The reproducibility of the NIRO 200 NX, NIRO 300, and the INVOS 5100c was similar (within-subject standard deviation 4.35%, 4.10% and 5.46%, respectively). In addition, these devices showed similar absolute oxygenation (rStO2) values (63% to 70%) and similar dynamic range. The OxyPrem showed significantly better reproducibility of 2.7%, but a somewhat lower absolute oxygenation (rStO2) value (60%) and dynamic range only two-thirds of the other three instruments (33). The results are comparable to earlier studies on the head regarding reproducibility and inter-instrument differences (32,34-37).

All eligible candidate NIRS devices for use in the SafeBoosC trial will be tested by the same procedure and should be within five percentage points in mean values and dynamic range in comparison with the above devices, and have a reproducibility of 6% or better. NIRS devices and sensors are non-sterile.

The SafeBoosC trial is a clinical investigation of benefits and harms of a range of different NIRS devices in combination with a treatment guideline. The trial is not designed to assess the performance of each NIRS device, since no reference standard is available in the preterm population. It will however evaluate whether each NIRS device is suitable for the trial population by careful collection of all adverse device effects.

Each participating centre is required to provide NIRS device(s) for the SafeBoosC trial. Each country shall apply with the regulations regarding the use of their device(s) in a clinical trial (e.g., a CE-mark that indicates use for the SafeBoosC trial population, as laid down by the national competent authority).

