**Figure 1: Trial design**

### 3.1 Randomisation

Participants will be randomised into either the experimental group or the control group. The allocation sequence will be computer-generated with a varying block size, and is kept concealed for all investigators. The ratio of allocation is 1:1. The randomisation will be stratified by the variable gestational age (low gestational age (<26 weeks) vs. high gestational age ( $\geq 26$  weeks)). Randomisation will be centralised at the Copenhagen Trial Unit and web-based.

Singleton infants will be randomised individually. Multiple birth infants will be randomised as a 'pair' or a 'group', i.e., all siblings will be allocated to the same treatment group. In centres, where only one or two cerebral monitoring devices are available, it may not be possible to include all infants from multiple-births. Thus, only one of a pair will be included or eventually only one or two if triplets. The sibling(s) enrolled will be the one(s) born last.

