#### **4.5 Recruitment feasibility**

Neonates are expected to be included from 12 neonatal intensive care units (NICUs) in 12 European countries. The units have estimated the likely rate of recruitment between 10 and 40 infants per year. The total is about 145-310 infants per year. The trial should therefore have good chance to be able to recruit 166 participants within a year. There are no defined minimum or maximum number of subjects to be included in each centre, since this is a phase 2 trial not powered to detect clinical outcome differences, but well-powered to detect the minimal clinical significant difference in rStO2.

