#### 8.1.4 Justification for recording and reporting periodicity and modality

The preterm patient population is a very seriously ill group. Most adverse events may be of a serious nature with or without the SafeBoosC trial intervention, and both intervention groups are expected to have a very high proportion of serious adverse events. It is therefore not possible, nor meaningful to record and report all adverse events. The following will be recorded and reported (for overview refer to table 4):

Adverse reactions (i.e. both expected (EAR) and unexpected (UAR) with a 'certain' or 'probable/likely' relation (see table 3) to the interventions will be recorded together with an assessment and reported with the trial results, The final report clinical investigation report to the competent authorities will summarize the ARs, including a discussion of causal relationship with investigational device, severity, and treatment needed.

Serious adverse events (SAE) to be recorded are: mortality; the mortality is high and will thus be analysed and reported as a secondary outcome measure and thus will not be reported to the authorities, and neonatal morbidities; these are believed to be the most important predictors for later development and health, and are recorded and reported as an outcome measure (necrotising enterocolitis stage 2-3, oxygen requirement, and

retinopathy of prematurity stage 3+ and above, as well as severe intraventricular haemorrhage and periventricular leucomalacia) thus not reported to the competent authorities.

Serious adverse reactions (i.e., both expected (ESAR) and unexpected (SUSAR) related to the cerebral oximeter and/or the treatment guideline will be recorded and analysed as a secondary outcome measure, but only SUSARs will subject to expedited reporting. Due to the nature of the population and the intervention, the near-incidents (**SAE-NI**) will be recorded, but not reported to the authorities.

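### The between-arm test of all-cause mortality at term is made conditional on a significant oximetry result, although the analysis of mortality is the stated reason for not reporting deaths to the authorities

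*Protocol*

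**What the plan says.** Section 10.2 specifies "two sided tests at the 0.05 level of significance". It tests the primary outcome (burden of hypo- and hyperoxia) first and then continues: "If the test is significant the three secondary outcomes (IBI at 64 hours, cUS, all cause mortality at term) will be tested using" an alpha of 0.05 with Hommel's adjustment across the three. Binary outcomes are analysed by logistic regression adjusted for gestational age category and site.

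Section 8.1.4 says of deaths: "the mortality is high and will thus be analysed and reported as a secondary outcome measure and thus will not be reported to the authorities". It treats severe intraventricular haemorrhage and periventricular leucomalacia, which are findings of the cerebral ultrasound outcome, in the same way. Table 4 agrees: neonatal mortality and morbidities are recorded and reported as an outcome measure, but are not reported to the authorities during the trial, yearly or at its end.

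Section 1.5.1 describes the aim: "The SafeBoosC trial is a clinical investigation of benefits and harms of a range of different NIRS devices in combination with a treatment guideline". Section 4.5 is open about size: "this is a phase 2 trial not powered to detect clinical outcome differences".

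**The concern.** An ordered test with a multiplicity adjustment protects claims of benefit from false positives. Applied to a possible harm, it can only lower the chance of seeing that harm. Here it is applied to the analysis that section 8.1.4 relies on in place of reporting deaths to the authorities.

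The worrying case is a guideline that leads to extra cardiovascular and respiratory interventions without lowering the burden. Section 9 itself allows that the intervention could be harmful. In that case the primary will usually be non-significant, and the rule gives no mortality test.

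The other safety routes described depend on individual causality judgements. Table 4 covers reactions graded certain or probable/likely, and section 8.3 limits the committee's stated remit to SUSARs with those grades. Where about one infant in five dies anyway, few deaths are likely to be attributed with that confidence. A modest excess would show mainly in the comparison between arms.

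**Working it through.** **Inputs.** Two-sided alpha 0.05 (10.2). Planned effect 0.30 and SD 0.50 on the log scale, power 95%, 75 per arm raised to 83 for twins (10.1 and Summary). Allocation 1:1 (3.1). Mortality about 20% (1.1). The protocol names no relevant excess of deaths, so 25%, 30%, 35% and 40% in the experimental arm are assumptions.

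**1. The plan's own figure.** n per arm = 2(1.960 + 1.645)² × 0.50² / 0.30² = 72.2, so 73 (about 74 with a t-test), against 75 stated. Power at 75 per arm is 0.957. Taking an average cluster size of 1.3, the twin step gives 150 × (1 + 0.3 × 0.33) = 164.9, against 166. Both agree closely enough, so 0.95 is used as the probability of a significant primary under the planned effect.

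**2. Mortality test on its own**, 83 per arm, 20% versus 30%, pooled z-test:

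- standard error under no difference: √(2 × 0.25 × 0.75 / 83) = 0.0672
- standard error under the alternative: √((0.20 × 0.80 + 0.30 × 0.70) / 83) = 0.0668
- power at 0.05: Φ((0.10 − 1.960 × 0.0672) / 0.0668) = 0.317, so 68.3% missed
- power at the strictest Hommel level, 0.05/3: Φ((0.10 − 2.394 × 0.0672) / 0.0668) = 0.181

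**3. Hommel over three outcomes.** In 20,000 simulated trials, power for 20% versus 30% is 0.185 if IBI and cUS have no effect, and 0.279 if each has about 80% power.

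**4. Adding the condition on the primary**, treated as independent of mortality:

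- planned effect on burden: 0.95 × 0.185 = 0.176 and 0.95 × 0.279 = 0.265, so 82.4% and 73.5% missed
- no effect on burden: the primary is significant in 5% of trials, so the excess is declared in at most 0.05 × 0.317 = 1.6%, and with Hommel in 0.9-1.4%

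| Assumed deaths, experimental arm (control 20%) | Missed, unconditional 5% test | Missed, planned effect with condition and Hommel | Declared at most, no effect on burden |
|---|---|---|---|
| 25% | 88.3% | 90.6-95.0% | 0.6% |
| 30% | 68.3% | 73.5-82.4% | 1.6% |
| 35% | 41.8% | 48.1-60.6% | 2.9% |
| 40% | 19.1% | 26.2-35.6% | 4.0% |

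**5. Share due to the rule.** For 20% versus 30% under the planned effect, the condition alone moves the miss rate from 68.3% to 1 − 0.95 × 0.317 = 69.9%. Condition plus Hommel adds 73.5 − 68.3 = 5.2 to 82.4 − 68.3 = 14.1 points.

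**6. What an interval would show.** With 20% deaths in both arms the 95% CI half-width is 1.96 × √(2 × 0.20 × 0.80 / 83) = 0.122. With 20% and 30% observed it runs from about −3 to +23 points. For 80% power at that difference about 294 infants per arm would be needed.

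Twin correlation is ignored in steps 2-6. At an effective 75 per arm, power in step 2 falls from 31.7% to 29.1%.

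**The case against.** The strongest reply is that section 10.2 restricts testing, not reporting. Table 4 and section 8.1.4 have mortality recorded and reported as an outcome with no condition on the primary, and the logistic model yields an effect estimate. Table 1 also collects mortality at 24 months. A reader might infer that mortality will appear only as an adjusted p-value, or not at all if the primary fails; the protocol does not say so. Nor does it say that non-significance will be read as absence of harm.

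A reader might also infer that the secondary analysis replaces all safety reporting of deaths. It does not. A death judged certainly or probably related is a serious adverse reaction, goes to the sponsor within 24 hours, and reaches the authorities in the yearly report or, if a SUSAR, by expedited report (8.1.5).

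The low power is disclosed in section 4.5, and no wording change can cure it. Mortality is also a hoped-for benefit (1.8), so ordered control of that claim is conventional. A separate analysis plan, not at hand, may settle how intervals are shown. The primary test is two-sided, so a clear worsening of the burden would also open the mortality test.

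All of this stands and limits the point. It does not remove it: the condition on the mortality test is a rule the protocol states, not a detail left open, and it makes no exception for harm.

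**Conclusion.** The point holds in a limited form. The rule places a harm comparison behind an efficacy result, while section 8.1.4 relies on that comparison to justify not reporting deaths to the authorities.

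The effect is large when the burden is unaffected. The test is then barred in about 95% of trials, and an excess is declared in under 2% for an assumed 20% to 30% rise, and in at most 4% over the assumed range of 25-40%.

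When the primary works as planned, the rule matters much less. It would be wrong to attribute the whole 74-82% miss rate to it, since about 68% is missed from sample size alone.

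These figures rest on 20% control mortality, the assumed excesses, 83 per arm, independence of the burden and mortality results, and no twin correlation.

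**What to change.** Add to section 10.2, for example:

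*The condition on the primary result and the Hommel procedure apply to claims of benefit only. All-cause mortality at term is compared between arms as a safety outcome whatever the primary result, as counts by arm and the effect estimate with an unadjusted two-sided 95% confidence interval. Absence of harm is not inferred from non-significance.*

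Severe brain injury on cUS can be handled the same way, because section 8.1.4 also exempts severe intraventricular haemorrhage and periventricular leucomalacia from reporting.

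The cost is one or two sentences, with no further patients or data. Error control for claims of benefit is unchanged. The downside is a slightly higher chance of a false alarm on harm, and an interval of about ±12 percentage points that shows plainly how little the trial can exclude.

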## 11. Data management

### 11.1 Data handling and archiving

All participant data are protected in accordance with the Danish Act on processing of personal data and the Danish Health Act. Source data will be registered in the participant's medical records or directly into the eCRF. A common web-based electronic case report form (eCRF) will be devised to enable a central database. Data entry into the central database handling of medical records is the responsibility of the investigators. Data will be stored in accordance with guidelines issued by the Danish Data Protection Agency, with which the trial will also be registered. After the establishment of a 'clean file', the database will be locked, data will be send for statistical analysis at the Copenhagen Trial Unit. The trial database will hereafter be kept according to the respective national laws. After end of trial, the data will be archived for five years according to good clinical practice guideline (appendix I).

At each trial-site the data flow (figure 5) will be monitored according to the GCP principles by a locally appointed external monitoring committee.

[figure not shown]

**Figure 5: The data flow in SafeBoosC**

After completion of statistical data analysis, data will be pseudo-anonymised and deposited at the Danish Data Archive. Also, data will be made available for other researchers by uploading a completely anonymised dataset onto ClinicalTrials.gov.

The investigator(s) permits trial-related monitoring, audits, regulatory inspection(s) by providing direct access to the source data and other relevant documents. Trial data will be handled according to regulations of data protection agency in the respective countries.

### 11.2 Medical coding

Adverse reactions (ARs) will be coded using MedDRA coding system by lowest level term (LLT), preterm term (PT), and system organ class (SOC). Concomitant medications will not be coded.

## 12. Quality assurance

The trial will be carried out in accordance with the Declaration of Helsinki in its latest form and the ICH GCP guidelines as well as national laws and regulations.

### 12.1 Monitoring

The trial will be monitored according to the ICH GCP guidelines, and a detailed monitoring plan will be developed. Centrally eCRFs will be checked, and as a minimum the following will be monitored locally:

- All patients for existence
- All patients for documented informed consent.

### 12.2 Device quality control

Each site is responsible for adhering to the quality control measures described in the oximeter manufacturer's users guidelines.

## 13. Trial and funding timeframe

| Trial stages                | Timeframe                                             |
|-----------------------------|-------------------------------------------------------|
| CIP development             | Spring 2011                                           |
| CIP finalised (first draft) | May 31, 2011                                          |
| Site selection              | Ongoing – depend on finance                           |
| Recruitment phase           | May 2012 – May 2014                                   |
| Assessment phase            | Last participant recruited (Primary outcome May 2014) |
| Final analysis              | 2015                                                  |

| Trial stages | Timeframe                            |
|---------------------|---------------------------------------------|
| Publication         | Late 2014 on primary and secondary outcomes |

| Funding                    | Timeframe                      |
|-----------------------------------|---------------------------------------|
| START                             | December 2010, awarded 183,848 DKK    |
| Danish Strategic Research Council | November 2011, awarded 11,100.000 DKK |

## 14. Legal aspects

### 14.1 Finance

The SafeBoosC project has received 183,848.00 DKK from the Danish Council for Strategic Research (DSF) under the Preparation of International Application (START) theme in December 2010. An application to the DSF seeking for 10,320,640.00 DKK under the Strategic Research in Individuals, Disease and Society theme, and was awarded 11,100,000.00 DKK November 2011. The sponsor/principal investigator [name] is the initiator of the SafeBoosC project. He has no financial interest in the results of the trial, nor the NIRS-instruments. He is not financially or in any other way involved in the Danish Council for Strategic Research.

